### Randomization and Blinding

Participants will be randomly assigned (1:1) to either the intervention group or the care-as-usual group. A computer-generated randomization sequence will be delivered, in an Excel (Microsoft Corp) file, to each recruitment site and will be concealed by one of the researchers by covering the allocation numbers with “black paint.” Randomization will be conducted and dated, per patient, by the researcher after the participant has signed the informed consent and baseline assessments have been performed.

Given the nature of the study, blinding of the researchers or participants during the behavioral intervention trial is not possible. However, the analysis of blood samples and all other outcome measures will be conducted by research team members who are blinded to the participants’ group assignment.

### Study Procedure

Approximately 2 weeks before completing CR, patients who have started the program will be approached by a research assistant for participation after eligibility (inclusion and exclusion criteria) has been checked by the local primary researcher or clinician. Patients who are eligible for CR but decide not to take part in the program will be approached after the research assistant is notified of patients’ participation status. If a patient expresses interest in participating, study information will be provided both verbally and in writing (patient information letter including the informed consent form).

For patients who consent to participate in the study, the baseline assessment includes physical exercise and functional tests, body composition analysis, blood draws (Multimedia Appendix 1), and completion of validated (web-based) questionnaires. Clinical data will be provided by the patient through an inquiry of selected data from the patient’s medical record. At 3 months, all participants will receive an online link to fill in a set of validated questionnaires to evaluate potential early changes that occur during the intervention. At 6 months, participants will be invited to the hospital to return the study devices (refer to the *Study Procedure* section) and undergo the second physical exercise testing, blood sampling, and questionnaire assessment (online). At 12 months, patients will be invited for the final hospital visit during which the same assessments as obtained at the 6-month follow-up will be performed. For patients who do not fill in the questionnaires within a given period of 10 days, up to 3 reminder phone calls will be made by the researcher.

### Study Objectives

#### Overview

The overall aim of the TIMELY study is to reduce the cardiac risk score through personalized health behavior change. The main focus is on the improvement of physical activity levels. All components of the TIMELY program should result in a reduction in the risk of recurrent cardiac events. All primary and secondary outcomes will be obtained at baseline; 6 months (the main outcome time point); and 12 months (long-term follow-up).

#### Primary Objectives

The primary objective of the TIMELY study is to investigate whether the TIMELY intervention is superior to usual care in terms of the following:

Reducing the risk of 10-year mortality assessed by a validated biomarker risk score (CoroPredict, primary biomedical outcome) from baseline to 6 months. The Coropredict score assesses cardiovascular risk using a combination of laboratory-based parameters (including hemoglobin A_1c_, N-terminal pro-B-type natriuretic peptide, high-sensitivity troponin I, cystatin C, and high-sensitivity C-reactive protein) and demographic information (age, sex, and smoking status) [35].Increasing the 6-minute walking test distance (primary behavioral outcome indicating functional fitness level) from baseline to 6 months.

#### Secondary Outcomes and Secondary Objectives

Improvements in the primary outcomes are expected to be associated with improvements in the following secondary outcomes:

Increase in physical activity: physical activity levels during daily life will be assessed using the International Physical Activity Questionnaire [36].Increase in cardiovascular exercise tolerance: measures of cardiovascular responses to exercise will be based on graded symptom-limited exercise tests, using maximum watt (watt/kg body weight) as the outcome.Healthy dietary habits: dietary habits will be assessed using the dietary questions from the validated Health Promoting Lifestyle Profiles-II questionnaire [37].Decrease in body weight: body weight will be measured in kilograms.Smoking cessation: smoking cessation will be assessed by the validated Fagerström questionnaire [38].Better medication adherence: medication adherence will be assessed using the validated Medication Adherence Report Scale questionnaire [39].Decrease in psychological stress levels: changes in psychological stress levels will be assessed using the Perceived Stress Scale [40].

The secondary objectives of the TIMELY project will be assessed using questionnaire data obtained at baseline and at 3, 6, and 12 months:

To investigate whether the TIMELY intervention is superior to care as usual in terms of improvement in physical and mental well-being and quality of life.To investigate the feasibility and usability of the TIMELY intervention.To investigate whether the TIMELY intervention is superior to care as usual in terms of cost-effectiveness.

### TIMELY Intervention

#### Development

The TIMELY intervention, including all technical components (dashboard, app, and monitoring devices), was co-designed with input from patients and health care professionals (eg, cardiologists, cardiovascular nurses, and therapists). A living laboratory approach was followed to collect detailed insights into patients’ needs and expectations on functionalities and app design. For a detailed description of the input provided by patients, refer to Douma et al [28] and Schmitz et al [41]. Furthermore, an extensive systematic review was conducted [29], which indicated that self-monitoring of behavior, prompts or cues, instructions on how to perform the behavior, goal setting, and social support were most likely to result in change in physical activity. In addition, the findings showed that providing prompts or cues as part of behavior change was unlikely to stimulate smoking cessation in patients with CAD and the intervention was adapted accordingly. The BCTs that were identified from focus groups and the systematic review were included in the TIMELY app throughout the functionalities of the app (chatbot, information provision, and monitoring).

#### Monitoring of Physical Activity, Hemodynamics, and Electrocardiogram During Daily Life Activities

All patients randomly assigned to the intervention group will be equipped with an activity tracker (Vivosmart 4, Garmin), an upper-arm BP monitor (Tel-O-Graph BT, IEM), and a 3-channel Holter monitor (netECG, livetec). Data from the activity tracker will be collected via Bluetooth on the patients’ smartphone and transmitted directly to the TIMELY-Net server (Semdatex) using an application programming interface provided by FitRockr to comply with European data protection regulations. The BP monitor will be placed in the patient’s home, together with a data transmission hub (eConnect, IEM), which allows secured mobile transmission of data (GSM standard) via the IEM gateway to the TIMELY-Net server. Collected data are then displayed in the TIMELY dashboard for case managers and made available to patients via the TIMELY app on their mobile phones, which can be downloaded from the app store for Android and iOS devices (see below for a detailed description of the TIMELY app).

Electrocardiogram (ECG) monitor data will be analyzed retrospectively after the trial. In brief, data will be downloaded from the ECG device at each participating center and uploaded to the TIMELY platform. The data will then be analyzed by ECG specialists at the participating partner institution, TU Dresden, using deep learning technology as described elsewhere [42]. Clinicians at the 3 centers will be involved to verify incidental findings of ECG abnormalities.

#### TIMELY Platform and Infrastructure

Data obtained from the monitoring devices and via the TIMELY app (patient-reported outcome measures [PROMs]) will be processed on the integrative TIMELY platform (Figure 2). The platform allows the assignment of devices to registered patients and provides insights into patients’ functioning and progress to designated case managers. The platform was designed to ensure that no personally identifiable data are transmitted over the internet. Specifically, services are executed on the same server cluster to significantly reduce the number of off-site accessible application programming interface end points. These end points are protected by up-to-date authentication methods (OpenID-Connect) and are encrypted in transit using Transport Layer Security. Personal identifiable data are also encrypted in the database. The clinician dashboard is implemented as a separate plug-in in a certified medical office software (inSuite, Doc Cirrus) hosted on a private cloud (which is a type of cloud computing environment that is dedicated to a single organization that offers CR with TIMELY) in the same local network as the other services of the TIMELY-Net platform. The platform follows a microservice approach to implement different services and functionalities, including the following:

Information from and to patients via the TIMELY mobile app (including messaging)Clinicians’ dashboard enabling case managers to assess structured patient data, definition of thresholds, and connected tasks or alerts as well as decision support systems (DSSs)Service to analyze 24-hour ECG data and detect cardiac arrhythmias such as atrial fibrillation (atrial fibrillation–detection)A chatbot to guide behavioral changeEcological momentary assessment service for assessment of PROMs via the mobile appEP DSSRisk prediction service to predict 10-year mortality risk in cardiovascular diseases (described in detail elsewhere) [43]

**Figure 2 figure2:**
[figure not shown]
TIMELY-Net infrastructure. AES: Advanced Encryption Standard; AF: atrial fibrillation; AI: artificial intelligence; DSS: decision support system; EMA: ecological momentary assessment; PROM: patient-reported outcome measure; SSL: Secure Sockets Layer; TLS: Transport Layer Security.

#### AI and Machine Learning

Demographic patient information and clinical data, including the ECG and exercise capacity results from the preceding clinic-based rehabilitation sessions, are entered into the risk profile database that is subsequently integrated and accessible to care providers and case managers via the TIMELY platform. Using machine learning–based algorithms, an optimal personalized exercise schedule is then developed and shared with the participants via the app (see below for details about the app). These exercise schedules are also adapted to the participant’s (changes in) actual activity levels over the past week to personalize the patient’s exercise levels during daily life activities.

AI is a key component of the TIMELY project as AI will support the modular, collaborative eHealth platform. AI is primarily directed toward the prediction of cardiac risk and complications. In addition, the targeted behavioral change interventions are designed to improve patients’ self-care and empowerment. AI will be primarily used to optimize risk prediction based on patients’ clinical and demographic background factors that will be integrated with the participants’ responses to the TIMELY eHealth intervention. The chatbot-based patient prompts will use preset and validated phrases, but not directly involve AI-based text, as this would create unpredictability of conversation content, which might be undesirable in patients with CAD. Thus, TIMELY involves a combination of AI-based risk prediction with patient-tailored personalized behavioral prompts via the chatbot. This approach will optimize long-term clinical care and secondary CAD prevention.

#### Clinical Dashboard

Information provided in the dashboard includes systolic and diastolic BP, heart rate, step count, floors climbed, calories burned, physical activities (type of activity, duration, and activity calories), sleep duration, and stress levels. Data can be displayed per day or as an average per week, or month. By setting alert thresholds on critical values such as missing data (ie, no data transmitted within 7 days), reported symptoms, or detected BP deviations, tasks are automatically generated with an indication of severity: high, medium, and low. These tasks help guide case managers in informing patients about changes in their health status that may require attention.

#### TIMELY App

The TIMELY app (available for Android and IOS devices) was developed following a simplistic design approach and serves two central purposes: (1) collecting self-report data or PROMs and (2) providing personalized information (from wearable or monitoring data) and advice regarding health behavior change (Figure 3). To achieve these goals, the app provides seven functionalities: (1) messaging function for nudging and information; (2) ecological momentary assessment diary assessment of symptoms, perceived stress, sleep quality, affective states, social behavior, motivation, and goal setting; (3) lifestyle and health information; (4) chatbot interaction guided by specific counseling techniques and methods; (5) weekly EP; (6) documentation and visualization of physical activity and vital signs; and (7) documentation and visualization of BP. The app was freely available for study participants and could be used by participants at their own time and pace.

The functionalities provided by the app (in combination with the microservices run on TIMELY-Net) are detailed in Textbox 1.

**Figure 3 figure3:**
[figure not shown]
TIMELY app functionalities (screenshot).

Functionalities of the TIMELY app.*Messaging function (“message center”)*: Patients can receive messages (push notifications), which are either sent manually by the case managers (technical feedback on the system, available updates, and instructions) or automatically generated messages. Automatic messages include information on available queries, feedback on achieved goals, and activity nudges. The activity nudges have a reminder function combined with health information and are generated from a large list of different messages to avoid redundancies. Nudging is integrated with weather information to suggest activity options—for example, “It's warm and sunny today, perfect for exercising outside”—and to help overcome barriers, such as “It's rainy today, but you can still enjoy a healthy indoor workout.” Moreover, geolocation nudging is used (based on GPS) to inform about the option to be physically active (“you are near a park, a good opportunity for a walk”).*Self-report assessments (“queries”) using ecological momentary assessment (EMA) diaries*: EMA (ie, brief diary-like questionnaires or “queries”) will be used for daily assessments of psychological and physical functioning and goal setting. This feature includes behavior change techniques (BCTs) such as self-monitoring of symptoms, perceived stress, sleep quality, mood states, health-related behaviors, and prompts or cues to provide responses.*Lifestyle and health information (“health education”)*: The app provides guideline-based information regarding cardiac health behaviors, benefits of regular physical exercise, and instructions on how to perform exercise (pictures and sample videos), medication, heart-healthy diet, stress management, smoking cessation, and risk factors selected by health care professionals (cardiologists, psychologists, and physical exercise specialists) using simple language. This section also provides web links to additional information provided by different societies and patient organizations. Several BCTs are part of this functionality, including *instructions on how to perform the behavior, information about health consequences, and demonstration of behaviors.**Chatbot interaction (“chat”)*: The TIMELY app includes a conversational agent that uses user context and artificial intelligence (AI)–based cardiovascular disease risk prediction information, referred to here as the “chatbot.” Suggestions from the chatbot are based on domain knowledge of behavioral intervention theories and related BCTs [44]. The chatbot primarily focuses on improving physical activity levels and overcoming potential barriers such as fatigue, psychological stress, or the patient’s environmental setting that interferes with or facilitates physical activity [45]. The chatbot also assists patients with planning health behaviors and identifying unhelpful behaviors and cognitions, including training modules to mitigate them based on cognitive behavioral interventions and motivational interviewing.*Exercise prescription (EP; “coach”)*: During the intervention phase, patients will receive a personalized, guideline-based EP with weekly updates. The EP is generated automatically using a decision support system (DSS) for case managers developed as part of the TIMELY project. The design, functionality, and validation of the tool will be described in detail elsewhere. In brief, the rule-based tool was developed in accordance with the European Society of Cardiology Guidelines on EP [46] and follows the frequency, intensity, time, and type of exercise approach. It is composed of 2 integral functionalities: the permissibility report and EP. The patient’s medical history and current exercise-related status inform the EP module, and information on sports to avoid or suitable sports disciplines and cautionary information to minimize the risk of injury or exercise-related cardiovascular problems are provided. The EP functionality suggests an initial exercise program and weekly progressions, relying on an algorithm crafted from best practices found in the clinical guidelines for exercise progression [47]. For initial exercise programs, the EP considers the fitness level of the patient after the phase-2 cardiac rehabilitation (CR), while for progressions, it factors success in achieving the caloric goals (metabolic equivalents, determined using the activity tracker based on heart rate) established in the previous week’s program and any reported symptoms. This approach ensures that the exercise regimen remains tailored to the individual’s needs and goals, promoting personalized exercise recommendations. Performed exercise sessions with duration and activity calories (as percent of the weekly goal) are provided. The EP incorporates the BCT of *action planning, instructions on how to perform the behavior, and biofeedback.**Goal setting and physical activity monitoring (“activity data”)*: Goal setting is a shared decision between the patient and case managers at the start. During the intervention, new goals are set by the case manager after receiving input from DSS. Patients are instructed to wear the activity tracker daily for 24 hours and wearing time (in percent) will be used (among other criteria) to define adherence to the program. Data on steps taken, physical exercise sessions performed (type, duration, activity calories, and percent of caloric goal), caloric expenditure, floors climbed, and heart rate are provided per day using simple, noncomplicated graphs. Data from previous weeks are provided for comparison and progress indication. For steps, a daily step goal is indicated in the graph. The step goal is discussed and defined with the patient during onboarding. Patients are informed about achievements via automated messaging weekly and can adjust the step goal if indicated using the diary function. This section of the app also provides feedback on set goals (eg, daily step goal) and goal achievement. The BCTs that are included in this feature are *biofeedback and feedback on outcomes of behavior.**Blood pressure (BP)*: Patients can review their current and past BP data via the app and will be instructed to use the BP monitor at the same time every day. Similar to physical activity monitoring, feedback on BP data is incorporated into this feature.

The chatbot uses predefined scripts that have been previously validated [45] and translated into German, Dutch, and Spanish by native speakers.

In addition, a support function providing technical help and troubleshooting, including written instructions and videos, is available in the app.

#### The Role of the TIMELY Case Manager

In alignment with a realistic health care setting, case managers (rehabilitation nurses and health care assistants) will provide technological and app-specific support during the study. During the inclusion period, patients are onboarded by the case manager, which includes giving access to the app and related monitoring devices and ensuring that participants understand the study requirements and all provided functionalities. The case manager sets the first weekly step goal together with the patient, and the patient agrees to the first EP (shared decision-making). Within the first week after inclusion, the case manager will contact the participants to verify proper installation of the app and monitoring devices, ensuring data collection integrity. Participants will have the opportunity to ask questions about the device functionality. During the intervention period (6-month follow-up), patients will be contacted monthly to ensure intervention delivery and resolve any unforeseen technical difficulties. These follow-up calls are strictly for technical support and continued engagement, with no behavior change support provided. The case manager’s actions are guided by a comprehensive handbook that includes protocols for missing data transitions and threshold violations.

For safety reasons, the case manager reviews new EPs generated by the EP DSS every Monday, before the EP is sent to the patient’s phone. The DSS has been developed to assist case managers in their daily work, primarily focusing on the identification of patients with deviating variables who require further assistance. The EP tool was designed to prescribe exercise to patients based on the medical guidelines, individual clinical profile, and personal needs. The tool allows for weekly adjustments based on the patient’s progress. EP additionally requires information on the previous (past week) exercise program, feedback on program execution (including metabolic equivalents achieved and reported symptoms), and patient preferences (if any) on which exercise parameters to increase or decrease (endurance or resistance, intensity, number of sets, and frequency). On the basis of these parameters, a prescription is produced. This DSS helps case managers in prescribing safe, well-informed, and patient-centered exercises. Depending on the task category, case managers can use various modes to contact patients. This includes sending (prewritten) messages via the app to guarantee data availability (“please wear your activity tracker regularly”) or calling the patient for safety reasons in case of an incidental finding (eg, BP deviations less than or greater than preset limits). Patients can also request a phone call with the case manager if they experience any technical problems or have questions about the app or monitoring devices.

#### Care as Usual

Participants randomly assigned to the care-as-usual group will receive standard care without any restrictions and will be allowed to seek additional care or assistance for lifestyle changes if needed. Participants in the control group will be asked to fill in questionnaires and undergo the same assessments as the intervention group.

### Statistical Analysis

For descriptive statistics, categorical variables will be compared with the *χ*^2^ test (Fisher exact test when appropriate). Continuous variables will be compared using independent sample *t* test or a nonparametric test where appropriate.

To address the main hypothesis, repeated measures ANOVA using generalized linear mixed modeling analysis will be used to investigate the effect of the intervention on changes from baseline to 6 months for the 2 primary end points (Coropredict score and a 6-minute walk test) using a 2 (intervention vs control)×2 (baseline to 6 months) design, accounting for potential baseline differences and correlations between baseline and 6 months assessments. Data for the primary outcomes will be analyzed according to the intention-to-treat principle.

For the secondary outcome measures, a similar approach will be used. To explore long-term effects at 12 months, 2 (group)×3 (repeated measure) mixed models will be used. In addition, univariable and multivariable regression analyses (both linear and logistic regression) will be used to examine cross-sectional and longitudinal associations between variables, with the type of regression analysis depending on the distribution characteristics of the variables.

Exploratory analyses will also include completer analyses and evaluation of trial adherence as related to the outcome measures. As this study includes multiple secondary outcome measures without correction for statistical type 1 error, the obtained results will be interpreted with caution and will primarily provide estimates of effect sizes related to the TIMELY intervention. Data will be analyzed using SPSS statistics (IBM Corp) [48] or equivalent.

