### Sample Size

A total of 360 patients will be enrolled across 3 participating centers: Hospital Universitario de Santiago de Compostela, Spain (120/360, 33.3%); Clinic Königsfeld of the German Pension Fund at the University of Witten/Herdecke, Ennepetal, Germany (120/360, 33.3%); and Elisabeth-TweeSteden Hospital, Tilburg, the Netherlands (120/360, 33.3%). At each center, patients will be randomly assigned, with 60 (50%) out of 120 receiving the intervention in addition to care as usual, and 60 (50%) receiving care as usual. Of 360 patients, 180 (50%) will receive the intervention, and 180 (50%) patients will receive care as usual.

On the basis of participation rates in previous randomized controlled trials [33], it is expected that approximately 33% of patients will decline participation. It is expected that a total of 480 patients will have to be approached to include 360 participants across the 3 study sites. Sample size calculations were based on medium-large effect sizes and statistical power analyses were conducted using G*Power (version 3.1.9.4; Heinrich-Heine-Universität Düsseldorf) [34]. A sample of 120 patients per center will enable detection of a medium effect size. The *f*^2^ for the between-within group interaction is 0.15 in a mixed model ANOVA, with a power of 0.80 and a two-sided α level of 0.025 (0.05/2, as two primary outcomes will be evaluated; details are provided in the *Study Objective* section). In brief, the set of variables for this analysis was based on a 2 (between-group: intervention vs control)×2 (repeated measures at baseline and 6 months) mixed model ANOVA, assuming sphericity and a correlation of 0.3 between the repeated measures.

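### The primary 2×2 group-by-time test reads most naturally as a change-score comparison; a baseline-adjusted analysis would be more precise and should be named

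*Protocol article*

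**What the plan says.** In the Statistical Analysis section, both primary outcomes (CoroPredict score and 6-minute walk distance) share one method: "repeated measures ANOVA using generalized linear mixed modeling analysis will be used to investigate the effect of the intervention on changes from baseline". The same sentence sets the second time point at 6 months, gives a 2 (group) × 2 (time) layout and ends with "accounting for potential baseline differences and correlations between baseline and 6 months assessments". It names no covariate, no ANCOVA and no constraint on the baseline means. A similar approach is planned for the secondary outcomes.

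The Sample Size section describes the same structure, a "2 (between-group: intervention vs control)×2 (repeated measures at baseline and 6 months) mixed model ANOVA", and powers its interaction. The effect size f² "for the between-within group interaction is 0.15 in a mixed model ANOVA". The test is planned "with a power of 0.80 and a two-sided α level of 0.025", and the calculation was done "assuming sphericity and a correlation of 0.3 between the repeated measures".

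The Randomization and Blinding section states that each patient is randomized "after the participant has signed the informed consent and baseline assessments have been performed".

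**The concern.** Baseline is one of the two levels of the repeated outcome. If each arm has its own free baseline mean, the group-by-time interaction is the difference between arms in mean change. That test uses part of the data to estimate a baseline difference that randomization makes zero in expectation. When the correlation between the two measurements is low, subtracting baseline adds more noise than it removes.

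At stake is the precision of both primary estimates and of the continuous secondary outcomes handled the same way. The estimate also becomes more sensitive to chance baseline imbalance. Recruitment closed at 358 patients, so the choice of analysis is one of the few remaining ways to gain precision.

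**Working it through.** **Inputs.** From Sample Size: ρ = 0.3, 180 per arm (360 planned), two-sided α = 0.025, power 0.80. Assumed here: equal SD (σ) at baseline and 6 months, and complete data unless stated otherwise.

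**The plan's own figure.** For the within-between interaction with two time points, λ = f²·N·2/(1−ρ). With f² = 0.15 this gives N = 26 for 80% power. Reading the 0.15 as f gives N = 152. Neither is the stated 120. That is a separate matter; what counts here is that the powered test is the interaction.

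**Is the interaction a change-score test?** In a simulated data set with 179 per arm and complete data, the 2×2 interaction and the t test on change both gave t = 4.323. Adding baseline as a covariate while it stayed an outcome left the interaction estimate at 0.537. The printed standard error fell from 0.124 to 0.112, but an identical estimator has the same sampling variance, so that fall is no real gain.

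**Variance per patient at ρ = 0.3.**
- Change score: 2(1−ρ)σ² = 2 × 0.7σ² = 1.40σ²
- 6-month value alone: 1.00σ²
- ANCOVA or common baseline mean: (1−ρ²)σ² = (1 − 0.09)σ² = 0.91σ²

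The ratio of adjusted to change-score variance is (1−ρ²)/[2(1−ρ)] = (1+ρ)/2 = 0.65, a saving of 35%. A simulation gave a ratio of 0.658.

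**Sensitivity of the saving.**

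| Condition | Saving |
|---|---|
| ρ = 0.3 | 35% |
| ρ = 0.5 | 25% |
| ρ = 0.7 | 15% |
| ρ = 0.8 | 10% |
| ρ = 0.3, baseline SD 0.8 to 1.25 times the 6-month SD | 22% to 50% |
| ρ = 0.3, 10% to 30% of 6-month values missing | 33% to 27% |

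For missing fraction p, the free-baseline mixed model has variance (1−ρ²)/(1−p) + (1−ρ)² and the common-baseline model has (1−ρ²)/(1−p), both in units of σ². At p = 0.3: 0.91/0.7 = 1.30, against 1.30 + 0.49 = 1.79, a saving of 27%. The missing fractions are assumptions; the article gives no dropout rate.

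**Detectable difference and power** (180 per arm, α = 0.025, ρ = 0.3, noncentral t).
- Difference detectable with 80% power: 0.386 SD (change score), 0.311 SD (adjusted).
- Power at a 0.50 SD difference, chosen only for illustration: 96.0% and 99.7%.
- Power at f = 0.15, which is a difference in change of 4 × 0.15 = 0.60 SD: 99.5% and above 99.9%.
- At f² = 0.15 as stated, power is close to 100% either way.

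**Chance imbalance.** A baseline difference D between arms moves the change-score estimate by (1−ρ)D in the opposite direction. For D = 0.2 SD the shift is 0.7 × 0.2 = 0.14 SD. The standard error of D is √(2/180) = 0.105 SD, so an imbalance of at least 0.2 SD in either direction has a probability of about 6%.

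**The case against.** The best defence is the clause "accounting for potential baseline differences and correlations between baseline and 6 months assessments". It could stand for a baseline-adjusted or common-baseline model, and then nothing is lost. The article is condensed, and the full protocol and SAP are not shown. This stands in part: the change-score reading is the most natural one but is not settled. The clause still does not settle it the other way, because it names no mechanism and one obvious implementation (baseline as both covariate and outcome) leaves the interaction unchanged.

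Second, the interaction test is valid under randomization, and the sample size was built on it, so plan and analysis agree. This stands. A reader might infer that the primary result would be biased or its type I error inflated. The documents do not support that: the shift above arises only given a chance imbalance and averages to zero over randomizations.

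Third, a reader might take 35% as the loss this trial will suffer. The 0.3 is a planning value, and the article gives no observed correlation for either outcome. CoroPredict includes age and sex, which hardly change in 6 months, so its correlation may well be higher and the saving smaller. It is equally tempting to show the power gap at a small effect such as 0.30 SD (56% against 77% at ρ = 0.3). The protocol does not plan for an effect that small, and at ρ = 0.7 the figures are 92% and 96%.

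Finally, two extensions go beyond the text. The variance formula does not cover smoking cessation if that is analysed as a binary outcome. And the article does not make adjustment depend on baseline significance tests; it mentions group comparisons only under descriptive statistics.

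**Conclusion.** The point holds as a recommendation on efficiency and clarity. The described 2×2 model most naturally yields a change-score comparison, and the article does not say how baseline enters. Because baseline precedes randomization, a valid and more precise analysis of the same data exists. With equal SDs, its advantage has the same direction at every ρ below 1. Its size depends on the true correlation, the ratio of the two SDs and the missing data, as the sensitivity table shows, so the 35% belongs to the planning value and should be quoted with its conditions. In practice the gain is a narrower interval and better power for modest effects. At the effects the protocol plans for, power is already high and the conclusion would rarely change.

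**What to change.** By a dated amendment before any unblinded comparison, state the primary analysis of both primary outcomes as one of the following:
- ANCOVA of the 6-month value on group and baseline value; or
- a linear mixed model with baseline and 6 months as outcomes and a common baseline mean for both arms.

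Report the adjusted between-group difference at 6 months with its confidence interval. Use the same model for the continuous secondary outcomes only. Do not enter baseline as a covariate in a model where it is also an outcome.

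If a baseline-adjusted model was intended all along, the same statement removes the ambiguity. No extra data or patients are needed. The cost is a documented amendment made after 6-month data collection has ended (complete by January 2025), so the record must show that it preceded unblinding.
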